## Abstract

**Introduction:**

Postoperative pulmonary complications (PPCs) represent a significant cause of postoperative morbidity and even mortality. However, there is a lack of consensus regarding this composite endpoint, the definition of the individual components, classification and optimal outcome measures. This study aims to refine the PPCs composite framework by evaluating its construct validity, assessing the necessity and risks of a composite measure and exploring the feasibility of differentiating severity categories.

**Methods:**

A Delphi consensus process will be conducted, engaging an international multidisciplinary group of 30–40 panellists, including clinicians, researchers, patients, public representatives and health economists. Through iterative rounds, the study will seek agreement on the individual components of the PPCs composite. Additionally, consensus will establish a framework for a composite outcome measure based on a standardised severity classification, appropriate timeframes and weighted grading of PPCs.

**Analysis:**

Consensus, defined by ≥75% concurrence in multiple choice questions or on Likert–scale statements, will be evaluated from round 2 onwards. Delphi rounds will be continued until all statements have reached stability of responses evaluated by χ^2^ tests or the Kruskal-Wallis test.

**Ethics and dissemination:**

The study will be conducted in strict compliance with the principles of the Declaration of Helsinki and will adhere to ACCORD guidance for reporting. Ethics approval has been obtained for this study from the University of Wolverhampton, UK (SOABE/202425/staff/3). Informed consent will be obtained from all panellists before the commencement of the Delphi process. The results of the study will be published in a peer–reviewed journal with the authorship assigned in accordance with ICMJE requirements.

**Trial registration number:**

NCT06916598 (clinicaltrials.gov).

STRENGTHS AND LIMITATIONS OF THIS STUDYThis Delphi study will engage a diverse and international panel of healthcare workers from Anaesthesiology, Surgery or Intensive Care Medicine involved in the management of patients with postoperative complications, as well as patients and patient care representatives, and health economists.The Delphi process will ensure the anonymity of the panellists and their voting process on the defining PPCs, to avoid any potential peer bias or group conformity.Variations in patients’ and patient care representatives’ preferences and differences in local or regional guidelines may influence panellists’ interpretation of statements and their opinions.

## Introduction

 Development of one or more postoperative pulmonary complications (PPCs) is linked to increased hospital length of stay and higher mortality rates,^1 2^ as well as substantial clinical and economic implications.^3 4^ Over the past decade, PPCs have increasingly been used in studies focussing on preventive perioperative measures, such as lung–protective intraoperative ventilation and postoperative respiratory support.^5^ The incidence of PPCs varies considerably across studies, likely due to factors such as the type of surgery and patient–related risk factors, but primarily because there is no uniform definition of this composite outcome.^5 6^

Several attempts have been made to define PPCs, typically expressed as a composite outcome that includes respiratory conditions, need for supplemental oxygen or mechanical ventilation, and complications such as intensive care unit (ICU) readmission and mortality.^5^ The European Perioperative Clinical Outcome (EPCO) definition, developed by a joint ESA–ESICM task force, identified variables for PPCs based on expert opinion but lacked a systematic literature review or formal consensus methodology, raising concerns about group conformity and bias.^7^,^9^ To address these limitations, the Standardised Endpoints for Perioperative Medicine (StEP) collaboration conducted a systematic review of pulmonary outcomes in perioperative patients, synthesising findings to inform a Delphi process.^10^ Unable to reach consensus on a universal definition, StEP proposed grouping PPCs by shared pathophysiology, such as pulmonary collapse and airway contamination.^8^ However, limitations included a lack of representation from low-resource settings, no patient involvement and potential bias due to non-anonymised voting and pre–final round discussions.^11 12^

Composite outcome measures can enhance statistical power by increasing event rates.^7^ However, they can obscure differences among individual components, as definitions often rely on binary outcomes without considering incidence, severity or varying diagnostic criteria. Variables such as respiratory infection, pleural effusion and aspiration pneumonitis differ in clinical significance and pathophysiology, complicating assessment. Inconsistent selection criteria and a lack of a universal definition hinder comparability across studies, potentially distorting reported incidence rates and intervention effects.^5^

When using the composite endpoint PPCs, it is crucial to consider the grading and hierarchical ranking of the individual components.^13^ Grading decisions, often based on experts’ opinions, patient input and economic insights, influence study results, underscoring the need for clear and consistent methodologies. The Clavien-Dindo classification system,^14^ although widely used for grading PPCs, has several limitations. This intervention–focused model has limitations when applied to PPCs, particularly in underestimating less severe complications that may only require observation.^15^ Furthermore, it lacks consistency across surgical specialities and has reduced applicability in low and middle-income countries (LMICs) due to variable resource availability and care practices.^16^ Importantly, it does not account for the long-term impact of complications on patients’ daily life and function.

Not all PPCs are of equal severity or clinical importance; for instance, severe respiratory failure might have more profound implications than a minor pleural effusion. Establishing a hierarchy among PPC components involves evaluating their relative severity and impact on patient outcomes. This ranking can help in interpreting the composite endpoints more meaningfully, distinguishing between minor and major complications.^17^ However, determining this hierarchy is not straightforward and often lacks standardisation.

The main objective of this international Delphi, named ‘Postoperative pulmonary complications—Evaluation for Consensus on Standardised Outcomes’ (PrECiSIOn), is to develop expert consensus on the definition of the composite PPCs and weightage grading of individual PPCs. Secondary objectives are to generate consensus on the timeframe and methods of monitoring PPCs. Specifically, we aim to develop a reliable, valid, feasible and universally accepted patient–centred definition of PPCs.

## Methods

### Design

PrECiSIOn is an international Delphi process that will be convened by a steering committee comprised of healthcare professionals with research experience in PPCs or postoperative respiratory failure, a patient care representative (SB), a health economist (RO) and a Delphi methodologist (PN). A diverse international panel will be invited based on predefined criteria. The members of the steering committee conducted a focused systematic search of the published literature between June 2018 and March 2025, using the PubMed and Embase databases to identify studies that reported PPCs as the primary or secondary outcomes. Our findings indicate that only two out of a total of 29 (7%) studies explicitly adhered to the EPCO or StEP definitions (table 1). The literature search will be used to inform the preliminary list of statements for the Delphi rounds, and the synthesis of the selected articles will be shared with the panellists. The steering committee members will organise iterative Delphi rounds, prepare and review the Delphi report, develop statements for subsequent Delphi rounds and provide controlled feedback to the panellists. The steering committee will not be allowed to vote in the Delphi rounds to avoid any bias.^11 18^ The results of this Delphi study will be reported using ACcurate COnsensus Reporting Document (ACCORD) guidelines.^19^

**Table 1 T1:** Studies identified through a focused systematic search using the postoperative pulmonary complications

Study	Publication year	PMID or DOI	EPCO or StEP	Symptoms	Diagnoses	Therapeutic consequences
He *et al*	2024	39256677			Atelectasis, respiratory failure, suspected or confirmed pneumonia	Prolonged mechanical ventilation, ICU re-admission
Li *et al*	2024	38374814			Atelectasis, pneumonia	Reintubation, need for bronchoscopy, death
Sahin *et al*	2024	10.4274/atfm.galenos.2024.82905		Bronchospasm	Atelectasis, respiratory failure, ARDS, suspected respiratory infection, pneumothorax, aspiration pneumonitis, pleural effusion	
Xuefei *et al*	2024	39278547		Bronchospasm	Atelectasis, respiratory failure, pneumonia, pneumothorax, aspiration pneumonitis, pleural effusion	
Admass *et al*	2023	37255746		Bronchospasm	Atelectasis, respiratory failure, suspected or confirmed pneumonia, ARDS, pneumothorax, aspiration pneumonitis, pulmonary congestion, pleural effusion, tracheobronchitis	

### Patient and public involvement

Individuals who have either personally experienced PPCs following surgery within the last 5 years or primary caregivers of such patients will be recruited as patient care representatives. Proficiency in English is required, and to mitigate potential bias, it is essential that the patient care representatives do not maintain a professional or advisory relationship with the steering committee or panellists. A concerted effort will be made to ensure a balance of geographical location, socioeconomic background, sex and ethnicity.

After obtaining informed consent, patients or patient care representatives will be engaged through structured interviews conducted by members of the steering committee and an independent qualitative research expert. A pilot-tested case vignette along with a Likert scale-based questionnaire will be employed to gather insights regarding the impact and severity of PPCs. The impact of the individual components of PPCs will be evaluated on a 7-point Global Rate of Change scale (from ‘very much worse’ to ‘very much better’) to calculate the minimal clinically important difference. Patient care representatives will be engaged in anonymous voting on the questionnaire. PPCs ranking and key themes synthesised from the interview will be shared with the panel in the second Delphi round, facilitating integration of patient perspectives into the consensus process. The interview data will be archived for a minimum of 5 years in a cloud server monitored by the Institutional Review Board of the approving organisation.

### Specific objectives

To generate consensus on the PPCs construct;

To generate consensus on the individual components of PPCs and their definition;

To generate consensus on the timeframe of monitoring for PPCs;

To generate consensus on the methods of monitoring PPCs, and

To generate consensus on the weightage grade of individual PPCs.

### Panellists

An international panel of 35–40 panellists from six continents, including patient representatives, will be invited to this Delphi study. A concerted effort will be made to include panellists from LMICs, as well as for an age and sex balance.

Panellists will be identified based on *either of* the following criteria:

At least 10 years of clinical experience as a staff member in Anaesthesiology, Surgery or Intensive Care Medicine with involvement in care of patients with postoperative complications.Author of at least three publications (observational studies or randomised clinical trials) using PPCs as a primary or secondary outcome.

The predefined selection criteria will facilitate a balanced composition of panellists possessing clinical or academic expertise in the field of PPCs. This approach will enhance the relevance, reliability and generalisability of the consensus findings. Panellists will be identified through a purposive sampling from the publications on PPCs and meeting the above–mentioned selection criteria. On confirming their acceptance, the panellists will be provided with a succinct summary of the Delphi process, explaining the role and objectives, expected schedule of Delphi surveys and duration required to complete each survey. To encourage continuing engagement of the panellists and to help prevent them from dropping out before completion of the full process, at least three personalised email reminders will be sent during each Delphi round, in addition to an effort to establish personal contact. Furthermore, all panellists will be recognised as collaborative authors in the final publication in appreciation of their professional expertise. Should the attrition rate of panellists exceed 20%, a sensitivity analysis will be conducted with the plausible worst–case and best–case scenarios, considering the opinion of non-responders.

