### Delphi rounds

Panellists and their responses will remain anonymised during the Delphi Rounds. Search results will inform the opening statements of the Delphi Rounds. The statements will be prepared on Google Forms as multiple–choice or 7-point Likert scales. Delphi round surveys will be presented to panellists through a unique online link. Multiple iterative Delphi rounds will be conducted until stable responses are achieved for all statements. Delphi round reports and patient–centred outcomes obtained from the interviews and questionnaire, as well as anonymised cumulative feedback, will be shared with panellists (figure 1).

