### Consensus and stability

Consensus for this Delphi study will be defined as ≥75% agreement (or disagreement) on the Likert scale, and for option(s) in multiple-choice statements. Stability of the responses will be calculated through non-parametric χ^2^ tests for multiple–choice statements and Kruskal-Wallis tests for Likert scale statements from round 2 onwards. A p value <0.05 will represent significant variation in the responses, and the statement will be repeated in the subsequent Delphi round. Open-ended responses from participants will be analysed using thematic analysis to identify recurring ideas and insights. Two independent researchers will code the data, with discrepancies resolved by discussion or a third reviewer. Open–text comments to survey questions will inform revisions to the questions for the subsequent Delphi rounds. Where more than 10% of responses include congruent comments on a particular item, the item will be modified for subsequent Delphi rounds.

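### The non-responder check runs only above 20% attrition, but a consensus verdict can already turn on non-responders at or below that level

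*Protocol article*

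**What the plan says.** The Panellists section ties the analysis of missing votes to a threshold: "Should the attrition rate of panellists exceed 20%, a sensitivity analysis will be conducted with the plausible worst–case and best–case scenarios". The views of those who did not answer are to enter these scenarios, but the section does not say how non-responders are assigned in either of them, and it states no check for attrition of 20% or less.

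The Consensus and stability section sets the decision rule: "Consensus for this Delphi study will be defined as ≥75% agreement (or disagreement) on the Likert scale", with the same threshold for multiple-choice options. The abstract repeats the 75% and starts the evaluation at round 2. Neither place says whether the percentage is of those who answered or of everyone enrolled.

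Panel size is 35–40 in the Panellists section and 30–40 in the abstract. The number of rounds is open: "Multiple iterative Delphi rounds will be conducted until stable responses are achieved for all statements". Losses can therefore build up over rounds.

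**The concern.** A worst-/best-case analysis asks whether a verdict would survive the votes that were not cast. Whether that matters depends on two things: how many votes are missing, and how far the statement lies from 75%. A single attrition cut-off ignores the second. A statement just over the line can be fragile at 10% loss, and a near-unanimous one can be safe at 20%.

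The consensus statements are the main product of this study, and the protocol names group conformity as a key ethical concern. If panellists who disagree with the emerging majority were more likely to leave, agreement among the remainder would rise without anyone changing their mind. The protocol gives no evidence that this will happen. At 20% loss or less, however, the plan as written would not show whether it could have mattered.

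**Working it through.** **Inputs.** Consensus threshold 75% (Consensus and stability; abstract). Trigger: attrition strictly above 20% (Panellists). Panel size N = 35–40 (Panellists) or 30–40 (abstract). The protocol derives no figure on this point, so there is nothing to reproduce.

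**Assumptions.** The 75% is counted among responders, and attrition is the share of the enrolled panel that is lost.

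**Notation.** m = panellists lost, r = N − m responders, a = responders who agree. Consensus is declared if a/r ≥ 0.75. Full-panel support then lies between a/N (no lost panellist would have agreed) and (a + m)/N (all would have). A statement is safe whatever the lost panellists think if a ≥ 0.75N, rounded up. Consensus on disagreement is the mirror image.

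**Step 1: at or below the trigger.**

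| N | Lost | Smallest consensus | Lowest full-panel support | Highest | Needed to be safe |
|---|---|---|---|---|---|
| 40 | 4 (10%) | 27/36 = 75% | 27/40 = 67.5% | 31/40 = 77.5% | 30/36 = 83.3% |
| 40 | 8 (20%) | 24/32 = 75% | 24/40 = 60% | 32/40 = 80% | 30/32 = 93.75% |
| 35 | 7 (20%) | 21/28 = 75% | 21/35 = 60% | 28/35 = 80% | 27/28 = 96.4% |
| 30 | 6 (20%) | 18/24 = 75% | 18/30 = 60% | 24/30 = 80% | 23/24 = 95.8% |

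No row exceeds 20%, so no check is triggered. With 8 of 40 lost, any statement with 24 to 29 of 32 in agreement (75% to 90.6%) is reported as consensus although its status could change.

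**Step 2: how many lost votes it takes.** A consensus statement falls below 75% of the panel once k lost panellists would not have agreed, where k is the smallest whole number above a + m − 0.75N.
- 24/32 with 8 lost: 24 + 8 − 30 = 2, so k = 3. Check: (24 + 5)/40 = 72.5%.
- 27/36 with 4 lost: 27 + 4 − 30 = 1, so k = 2. Check: (27 + 2)/40 = 72.5%.
- 29/32 with 8 lost: 29 + 8 − 30 = 7, so k = 8, which is all of them.

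All three statements would be reported alike, but they differ widely in fragility.

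**Step 3: above the trigger, if every non-responder is counted against (N = 40).**
- 9 lost (22.5%): 30/31 = 96.8% needed.
- 10 lost (25%): 30/30 = 100% needed.
- 11 lost (27.5%): unanimity gives 29/40 = 72.5%, so nothing can pass.

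In general the highest attainable share is 1 − d at attrition d, which is below 75% once d > 25%.

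**Step 4: a milder worst case.** If a fraction q of non-responders is assumed to agree, responders must reach (0.75 − dq)/(1 − d). At d = 30%:
- q = 25%: (0.75 − 0.075)/0.70 = 96.4%.
- q = 50%: (0.75 − 0.15)/0.70 = 85.7%.

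So a statement can pass above 25% attrition.

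**Step 5: the best case above the trigger.** With 12 of 40 lost (30%), 18/28 (64.3%) reaches (18 + 12)/40 = 75%, while 17/28 (60.7%) reaches only 29/40 = 72.5%. The best case still separates statements that fail whatever the lost panellists think from those that might have reached consensus.

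**The case against.** A prespecified attrition trigger is a legitimate design choice. The protocol also works to keep panellists: at least three personalised reminders per round, personal contact and collaborative authorship. Panellists vet the final statements. An article may leave the assignment rule for missing votes to a fuller document, so its absence here is not in itself a fault. All of this stands, but none of it shows whether a given verdict depends on the votes that were lost at 20% or less.

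The 60% figure can be called a corner case, since it needs exactly 20% loss, exactly 75% agreement and every lost panellist dissenting. That is fair for the figure. The verdict, however, changes well before that extreme: three dissenters among the eight lost are enough for a 24/32 statement.

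The denominator is a real uncertainty. If the 75% were of all enrolled panellists, 24 of 40 would not be consensus and the point about the trigger would fall away. A separate analysis "considering the opinion of non-responders" makes better sense if they are outside the main count, but the text does not say so.

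A reader might also infer that above 25% attrition no statement can pass and the result of the analysis is known in advance. The documents do not support this. They speak of a *plausible* worst case and nowhere say that every non-responder counts against. A milder rule lets statements pass (Step 4), and the planned best case remains informative (Step 5).

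**Conclusion.** The concern holds in a limited form. On a responder denominator, the trigger leaves unchecked a range of attrition in which consensus can turn on non-responders. At 20% loss, a statement at the threshold may have 60% to 80% support in the full panel, and with N = 40 only those at 30/32 (94%) or more are safe. At 10% loss, 75% among responders may be 67.5% of the panel.

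The 25% limit is conditional: it applies if, and only if, the worst case counts every non-responder against. The protocol leaves that scenario undefined.

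Two further inferences go beyond the documents. No expected attrition is given, so it cannot be said that losses will probably fall at or below 20%. No distribution of agreement is given either, so the share of statements that would be fragile is unknown.

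**What to change.** Remove the 20% trigger. State whether the 75% is of responders or of all enrolled panellists. For every statement, at any attrition, report a tipping point:
- for a statement that reached consensus, the number of non-responders who would have to disagree for it to fall below 75% of the panel;
- for one that did not, the number who would have to agree for it to reach 75%.

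Flag every statement whose status could change. This needs no earlier rating and no assumption about what non-responders think.

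Carrying forward a panellist's last rating can be a supplementary scenario, but only where the item wording is unchanged and responses can be linked across rounds. The protocol allows items to be reworded after congruent comments, and it does not say that the anonymised responses can be linked.

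The cost is a simple count per statement and a sentence or two in the plan. The downside is that some consensus statements will be published with a label of fragility. No further data collection is needed.

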### Delphi rounds

Panellists and their responses will remain anonymised during the Delphi Rounds. Search results will inform the opening statements of the Delphi Rounds. The statements will be prepared on Google Forms as multiple–choice or 7-point Likert scales. Delphi round surveys will be presented to panellists through a unique online link. Multiple iterative Delphi rounds will be conducted until stable responses are achieved for all statements. Delphi round reports and patient–centred outcomes obtained from the interviews and questionnaire, as well as anonymised cumulative feedback, will be shared with panellists (figure 1).

**Figure 1 F1:**
[figure not shown]
Steps of the Delphi process employed for the study. PPCs, Postoperative pulmonary complications, created in BioRender.com.

